## Abstract

**Background:**

Liver surgery in perihilar cholangiocarcinoma (PHC) is associated with high postoperative morbidity because the tumor typically causes biliary obstruction. Preoperative biliary drainage is used to create a safer environment prior to liver surgery, but biliary drainage may be harmful when severe drainage-related complications deteriorate the patients’ condition or increase the risk of postoperative morbidity. Biliary drainage can cause cholangitis/cholecystitis, pancreatitis, hemorrhage, portal vein thrombosis, bowel wall perforation, or dehydration. Two methods of preoperative biliary drainage are mostly applied: endoscopic biliary drainage, which is currently used in most regional centers before referring patients for surgical treatment, and percutaneous transhepatic biliary drainage. Both methods are associated with severe drainage-related complications, but two small retrospective series found a lower incidence in the number of preoperative complications after percutaneous drainage compared to endoscopic drainage (18-25% versus 38-60%, respectively). The present study randomizes patients with potentially resectable PHC and biliary obstruction between preoperative endoscopic or percutaneous transhepatic biliary drainage.

**Methods/Design:**

The study is a multi-center trial with an “all-comers” design, randomizing patients between endoscopic or percutaneous transhepatic biliary drainage. All patients selected to potentially undergo a major liver resection for presumed PHC are eligible for inclusion in the study provided that the biliary system in the future liver remnant is obstructed (even if they underwent previous inadequate endoscopic drainage). Primary outcome measure is the total number of severe preoperative complications between randomization and exploratory laparotomy. The study is designed to detect superiority of percutaneous drainage: a provisional sample size of 106 patients is required to detect a relative decrease of 50% in the number of severe preoperative complications (alpha = 0.95; beta = 0.8). Interim analysis after inclusion of 53 patients (50%) will provide the definitive sample size. Secondary outcome measures encompass the success of biliary drainage, quality of life, and postoperative morbidity and mortality.

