#### Sample size

Determination of the sample size is split in a provisional and definitive calculation, because only little retrospective evidence is currently available for power estimation. A previous study from the primary study center showed a severe complication rate of 60% in the EBD group versus 18% in the PTBD group. In the DRAINAGE trial, a complication rate of 50% is expected after EBD and 25% after PTBD (i.e. a relative decrease of 50%). This estimation was further expanded with proportions for the number of complications, as shown in Table 4. Accounting for a 3% dropout, 53 patients are needed in each arm resulting in a provisional required sample size of 106 patients (Wilcoxon/Mann–Whitney rank-sum test for ordered categories; α = 0.95; β = 0.8).

**Table 4 Tab4:** **The estimated number of complications in each study group used to calculate the provisional sample size**

	EBD	PTBD
0 complications	50%	75%
1 complication	25%	17%
≥2 complications	25%	8%
Total proportion	100%	100%

The estimated proportion of patients is presented for each categorical number of complications.

Interim analysis after inclusion of 53 patients (50%) will provide the definitive sample size, which will be calculated based on the observed number of complications in the EBD group. The definitive sample size will be determined similar to the provisional sample size, again using a relative decrease of 50% in the proportion of complications unless the absolute decrease drops below 20%, which is defined as the lowest absolute decrease with clinical relevance.

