#### Data analysis

The principal analysis consists of an intention-to-treat comparison of the number of preoperative severe drainage-related complications. The research hypothesis will be evaluated using a Wilcoxon/Mann–Whitney rank-sum test with a two-sided 0.05 significance level. The comparison will be expressed in terms of a relative risk and 95% confidence intervals, as determined with multinomial logistic regression.

Subsequent analyses are directed at the secondary endpoints. Continuous data will be presented as the mean with standard deviation or median with interquartile range depending on data distribution, and accordingly evaluated with Mann–Whitney U or t-test statistics. Categorical variables will be evaluated using Pearson’s chi-squared test or Fisher’s Exact test as applicable.

Preplanned subgroup analyses will be based on a dichotomized complication rate to retain statistical power (no complication versus 1 or more complications), and the analyses will consist of logistic regression with the subgroup and randomized treatment added as an interaction term. Subgroup analysis will be performed for patients with Bismuth type 4 tumors, and patients with a left-sided FLR.

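### The 106 patients follow from Table 4 at two-sided alpha 0.05 and 80% power, but alpha and beta are misprinted and the abstract's 50% decrease in number is not the effect that was powered

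*Protocol article*

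**What the plan says.** All references are to the Protocol article.

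- **Abstract, Methods/Design:** "a provisional sample size of 106 patients is required to detect a relative decrease of 50% in the number of severe preoperative complications", followed by "alpha = 0.95; beta = 0.8".
- **Sample size:** the expected complication rate is 50% after endoscopic drainage (EBD) and 25% after percutaneous drainage (PTBD), and this is called a relative decrease of 50%. Then: "This estimation was further expanded with proportions for the number of complications, as shown in Table 4". Table 4 gives 50/25/25% for EBD and 75/17/8% for PTBD, for 0, 1 and at least 2 complications. With 3% dropout this leads to 53 per arm, 106 in total, by a "rank-sum test for ordered categories; α = 0.95; β = 0.8".
- **Sample size, definitive calculation:** after 53 patients the size is recalculated from the observed EBD complications, "again using a relative decrease of 50% in the proportion of complications", unless the absolute decrease falls below 20%.
- **Data analysis:** a "rank-sum test with a two-sided 0.05 significance level".

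**The concern.** There are two separate faults.

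First, an alpha of 0.95 is a 95% false-positive rate, and a beta of 0.8 is 20% power. Neither fits the Data analysis section. A reader cannot tell from the printed values which error rates the design used.

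Second, the primary outcome is a count, tested as ordered categories, and the abstract attaches the 50% to that count. Table 4 halves something else: the proportion of patients with at least one complication. It adds a shift from two or more complications towards one, which the text does not explain. The rank-sum test draws power from that shift, so the claimed 80% holds for Table 4 and not for every 50% decrease.

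The same gap carries into the definitive calculation. That rule takes the EBD data as observed and halves the proportion, but does not say how the PTBD proportion divides between one and two or more complications. At the same EBD distribution as in Table 4, this choice alone moves the total by 20 patients.

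**Working it through.** **Inputs.** Table 4 proportions, 3% dropout and equal arms (Sample size); rank-sum test at two-sided 0.05 (Data analysis); power 0.80, reading the printed 0.8 as power.

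**Formula.** n per arm = (z_α√V0 + z_β√V1)² / (θ − 0.5)². Here θ is the probability that an EBD patient has more complications than a PTBD patient, plus half the probability of a tie. V0 = (1 − Σp̄³)/6 is the tie-corrected null variance, with p̄ the average proportion per category. V1 is the variance under the alternative: the sum, over the two arms, of the variance of each patient's mid-rank position in the other arm.

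**Step 1: reproduce 106 from Table 4.**
- θ = 0.50×0.75/2 + 0.25×(0.75 + 0.17/2) + 0.25×(0.75 + 0.17 + 0.08/2) = 0.1875 + 0.20875 + 0.24 = 0.63625.
- p̄ = 0.625, 0.21, 0.165; Σp̄³ = 0.2579; V0 = 0.1237; V1 = 0.1124.
- n = (1.960×0.3517 + 0.8416×0.3353)² / 0.13625² = 50.8, so 51.
- 51/0.97 = 52.6, so 53 per arm and 106 in total. This matches exactly.
- Simulated power (200,000 trials) is 80.4% with 51 per arm.

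Using the null variance alone gives 53 before dropout and 55 after (110 in total). One-sided versions give 42 to 44 per arm after dropout.

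**Step 2: the printed values.** With alpha = 0.95 two-sided and power 0.20, the bracket is 0.063×0.352 − 0.842×0.335 = −0.26, so no meaningful sample size results. The printed figures are 1 − alpha and power under the wrong labels.

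**Step 3: what Table 4 assumes.**

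| | EBD | PTBD | Relative decrease |
|---|---|---|---|
| Any complication | 50% | 25% | 50% |
| Exactly 1 | 25% | 17% | 32% |
| 2 or more | 25% | 8% | 68% |
| Mean count, 2 or more scored as 2 | 0.25 + 2×0.25 = 0.75 | 0.17 + 2×0.08 = 0.33 | 56% |

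If the top category averages 3 in both arms, the decrease in the mean is 59%. If it averages 2 under EBD but 2.56 under PTBD, the decrease is 50%, since (0.375 − 0.17)/0.08 = 2.56.

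**Step 4: halve every category (PTBD 75/12.5/12.5).**
- Mean count: 0.125 + 2×0.125 = 0.375, half of 0.75.
- θ = 0.1875 + 0.25×0.8125 + 0.25×0.9375 = 0.625; V0 = 0.1238; V1 = 0.1152.
- Simulated power is 72.6% with 51 per arm and 74.3% with 53.
- For 80% power: n = 60.9, so 61; 61/0.97 = 62.9, so 63 per arm and 126 in total (130 with the null variance alone).

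**Step 5: other ways to halve the mean (2 or more scored as 2, 51 per arm).** PTBD 67.5/27.5/5 gives 64% power; 72.5/17.5/10 gives 70%; 77.5/7.5/15 gives 75%; 81.25/0/18.75 gives 80%. Patterns with still fewer patients in the top category go lower, to about 59% for 62.5/37.5/0.

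**The case against.** The strongest reply is that the body defines the 50% plainly, as a complication rate falling from 50% to 25%. Table 4 matches that definition and is printed in full, and 106 follows from it. The abstract's Background also speaks of the number of complications and then reports percentages, so its sample-size sentence may mean the same. The mislabelled alpha and beta change neither the test nor the sample size. The 106 is provisional, the definitive calculation is to resemble it, and the full protocol may give the split.

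Most of this stands, and it rules out some readings that a reader might be tempted to make:

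- **That 106 is miscalculated or too small.** It is neither for the effect defined in the body.
- **That Table 4 implies at least a 56% decrease in number.** This needs the top category to average no more under PTBD than under EBD. The documents do not give those averages.
- **That power for a true halving of the number is 73%.** That figure belongs to one pattern. A halved mean does not fix the power of a rank test.

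The reply does not remove three things. The abstract names a different effect from the one powered. The text gives no reason for the 68% drop in patients with two or more complications. And resemblance to the provisional calculation does not define the split, because no formula for 17/8 is stated. A fuller protocol may settle the split, so that part is a request to state it where the rule is printed.

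**Conclusion.** The point holds as a correction of labels and of the stated effect. The printed alpha and beta are wrong in both places and conflict with the Data analysis section, with no effect on the sample size. The abstract ties the power to a 50% decrease in number, whereas the design is powered for the Table 4 distribution, where the mean count falls by about 56% if two or more is scored as 2 in both arms. Power is 80% under Table 4 and about 73% if each category is halved, both with 51 evaluable patients per arm. Over other patterns that halve the mean under the same scoring it runs from the low 60s, or slightly below at the extreme, up to about 80%. These figures assume the tie-corrected rank-sum test at two-sided 0.05 and the EBD column of Table 4.

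**What to change.** 1. In the abstract and under Sample size, print: two-sided alpha = 0.05, power = 0.80 (beta = 0.20).
2. In the abstract, state that the 50% decrease is in the proportion of patients with any severe complication, under the Table 4 distribution.
3. Under Sample size, give the reason for the 17/8 split and state that power is about 73% if every complication category is halved.
4. Before interim data are seen, write down how the PTBD proportion will be divided between one and two or more complications in the definitive calculation. Keeping Table 4's ratio is one option: 17/25 = 68% with one and 8/25 = 32% with two or more, among PTBD patients with any complication.

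Items 1 to 3 cost wording only, and no patients need to be added to the provisional 106. Item 4 is free in itself, but the rule chosen has a price. With EBD as in Table 4, the Table 4 ratio leaves the total at 106, while halving each category would raise it to about 126.

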**Discussion:**

The DRAINAGE trial is designed to identify a difference in the number of severe drainage-related complications after endoscopic and percutaneous transhepatic biliary drainage in patients selected to undergo a major liver resection for perihilar cholangiocarcinoma.

**Trial registration:**

Netherlands Trial Register [NTR4243, 11 October 2013].

**Electronic supplementary material:**

The online version of this article (doi:10.1186/s12876-015-0251-0) contains supplementary material, which is available to authorized users.

## Background

Perihilar cholangiocarcinoma (PHC) is a biliary malignancy originating at or near the hepatic duct confluence that typically causes biliary obstruction with concomitant cholestasis [1]. Surgical resection of PHC, using a combined extrahepatic bile duct resection and partial liver resection, offers the best chance for long-term survival with a reported median survival of 19–39 months in large series [2]. However, liver surgery in cholestatic patients with PHC is associated with high risks of postoperative morbidity and mortality, as reported up to 68% and 18%, respectively [3,4].

Preoperative biliary drainage is used to create a safer environment for liver surgery in PHC [5]. It reduces jaundice, improves nutritional status and liver function, reduces bacterial translocation, and improves the ability of the liver to regenerate postoperatively [6]. Owing to these effects, preoperative biliary drainage has been shown to reduce postoperative mortality, especially in extended liver resections [7]. Nonetheless, biliary drainage can be harmful when drainage related complications further deteriorate the patients’ condition or increase the risk of postoperative morbidity [8-10]. These complications potentially outweigh the benefits of biliary drainage, and should be minimized in order to optimize surgical outcomes.

The two most commonly used drainage techniques are endoscopic biliary drainage (EBD) or percutaneous transhepatic biliary drainage (PTBD). EBD is often used to treat symptoms of jaundice in regional centers before referral to specialty centers for surgical management. However, preoperative EBD in PHC is associated with a high rate of complications such as cholangitis and pancreatitis. As an alternative, PTBD reportedly has a high rate of technical success and theoretically, is associated with a lower incidence of cholangitis because there is no retrograde bacterial contamination from the gut. Nonetheless, other drawbacks have been reported of PTBD including hemorrhage, catheter dislocation, and patient discomfort. Only two small retrospective series (n = 68 and n = 101) have compared the incidence of preoperative complications, consistently reporting fewer complications after PTBD compared to EBD (18-25% versus 38-60%, respectively) [11,12]. These studies were obviously flawed by their retrospective study design and heterogeneity in procedure-site (i.e. regional versus specialty center). Prospective studies are needed to confirm the potential benefit of preoperative PTBD compared to EBD.

The present study randomizes patients between preoperative EBD and PTBD. Patients are eligible for inclusion when they have presumed PHC on imaging, when they are selected to potentially undergo a major liver resection, and when they have biliary obstruction in the future liver remnant (FLR). The study is based on an “all-comers” design, so patients may also be included if they require additional preoperative biliary drainage after previous inadequate EBD in a regional center before referral. The primary outcome measure of the study focuses on the total number of severe preoperative drainage-related complications.

## Methods/Design

### Study objectives

The aim of this study is to compare EBD and PTBD in terms of the total number of preoperative severe drainage-related complications (primary outcome), the success of biliary drainage, quality of life, and postoperative morbidity and mortality.

### Design

The present study is a multicenter randomized controlled superiority trial. Patients are randomized to preoperative EBD or PTBD by minimization using computer-generated allocation (www.tenalea.net). The randomization procedure is stratified for three factors, including: (attempted) biliary drainage procedures before referral to the enrolling center (drainage naïve versus drainage non-naive); the level of bile duct involvement (Bismuth type 1, 2, 3A or 3B versus type 4); and enrolling center.

### Ethics

This study is conducted in accordance with the principles of the Declaration of Helsinki and the Dutch Medical Research Involving Human Subjects Act. The medical ethical committee of the Academic Medical Center in Amsterdam approved the protocol on September 2, 2013. An addendum to the protocol was approved March 5, 2014. Secondary approval was sought from all local ethics committees. Informed consent is obtained from each participating patient in oral and written form prior to randomization. The DRAINAGE trial is registered in the Dutch Trial Register with identification number NTR4243.

### Study population

The study is based on an “all-comers” design. All patients with presumed PHC, who are selected by the multidisciplinary team meeting at one of the enrolling centers to potentially undergo a major liver resection, are eligible for inclusion in the study when they have biliary obstruction in the FLR.

#### Inclusion criteria

According to the 7th edition of the American Joint Committee on Cancer staging, PHC is defined as a tumor originating in the common hepatic duct, the hepatic duct confluence, or in the left or right hepatic duct. [1]. The latter category may also include patients with an intrahepatic tumor that invades the hepatic duct confluence. Pathologic confirmation of PHC is not required prior to inclusion in the study. Patients are selected to potentially undergo a major liver resection if preoperative imaging with CT and/or MRCP shows a resectable tumor without evidence of distant metastases (including lymph node metastases beyond the hepatoduodenal ligament) [1]. Portal vein resection and reconstruction may be required to obtain tumor-free resection margins.

Biliary obstruction in the FLR is separately defined for patients with or without previous EBD procedures (Table 1). For drainage naïve patients, it is defined as a total bilirubin level of at least 50 μmol/L. For patients with previous EBD procedures, it is defined as a persistently rising total bilirubin level above 50 μmol/L (i.e. no stent placed or insufficiently draining stent) or as persistent biliary dilatation in the FLR on imaging (i.e. previous stent placed in contralateral side of liver).

**Table 1 Tab1:** **Definitions of biliary obstruction in the future liver remnant**

Patient type	Definition of inadequate biliary drainage
Drainage naïve	Serum Bilirubin >50 μmol/L.
Drainage non-naïve	Persistently rising total bilirubin level above 50 μmol/L (i.e. no stent placed or insufficient draining stent).
	Persistent biliary dilatation in the FLR on imaging (i.e. previous stent placed in contralateral side of liver).

Patients are ‘drainage non-naïve’ if they underwent previous (attempted) EBD before referral to one of the enrolling centers.

#### Exclusion criteria

Since the primary outcome measure focuses on complications, patients are not eligible for inclusion if they have incompletely recovered from any side effect of previous biliary drainage procedures. Patients are required to be off antibiotic treatment for at least 5 days. Other exclusion criteria include any contra-indication for major liver surgery (e.g. ECOG/WHO score ≥3), technical contra-indication for either EBD or PTBD (e.g. previous gastrojejunostomy), or refusal to provide informed consent.

### Primary outcome measure

The primary outcome is the total number of severe drainage-related complications measured between randomization and exploratory laparotomy. The study is designed to detect superiority of PTBD. Some patients lose eligibility to undergo major liver resection before exploratory laparotomy (e.g. distant metastases found at staging laparoscopy, deterioration of the patients’ condition, or diagnosis of benign disease precluding the need for surgical therapy). For these patients, the number of drainage-related complications is measured until 7 days after the decision to cancel exploratory laparotomy, or until 90 days after randomization (whichever comes first).

A severe complication is defined as any complication related to the drainage procedures, leading to an additional invasive intervention, (extended) hospitalization, or death. Definitions for potential severe drainage-related complications, as evaluated in previous studies, [11,13] are shown in Table 2.

**Table 2 Tab2:** **Definitions of severe complications in the primary outcome measure**

Severe complication	Criteria
Cholangitis	Elevation in temperature more than 38,5°C and Leukocytes ≥10 *10^9^/L, thought to have a biliary cause, without concomitant evidence of acute cholecystitis, requiring invasive intervention.
Acute cholecystitis	Radiologic evidence of cholecystitis, elevation in temperature more than 38.5°C and Leukocytes ≥10*10^9^/L, and requirement of percutaneous drainage or emergency cholecystectomy.
Stent/ catheter dysfunction	Rising bilirubin level after therapeutic success had initially been obtained, without signs of cholangitis or cholecystitis, requiring new cannulation of the tumor.
Acute pancreatitis	Abdominal pain and a serum concentration of pancreatic enzymes (amylase or lipase) ≥3 times the upper limit of normal, that requires ≥1 one night of hospitalization.
Hemorrhage	Clinical evidence of bleeding with the need of a blood transfusion.
Perforation	Retroperitoneal or bowel-wall perforation documented by any radiographic technique requiring intervention.
Portal vein thrombosis	Clinical evidence of thrombosis confirmed on colour Doppler US as absence of flow compatible with occlusion, precluding liver surgery.
Dehydration	Severe dehydration with electrolyte disturbances resulting from excessive fluid loss through externally draining catheters, requiring rehydration in the clinical setting.

To exclude bias in determining events pertaining to the primary outcome measure, a blinded adjudication committee will review all events and evaluate whether events count as severe complication according to the proposed definitions.

### Secondary outcome measures

Secondary outcome measures will be used to select the preferred method if there is no difference in the primary outcome at conclusion of the study. Secondary outcome measures include:The separate incidence of preoperative cholangitis;The number of drainage procedures required to achieve technical success;The proportion of patients with therapeutic success at 7 days after technical success;The total number of drainage procedures that involved (attempted) stent (re-) placement;The proportion of patients requiring crossover treatment;Interval bilirubin decrease at 7 days and 14 days after biliary drainage relative to the bilirubin level at randomization;The number of patients with rescheduled or cancelled laparotomy due to severe drainage-related complications;Quality of life, measured with the EORTC Quality of Life Questionnaire C-30 (QLQ-C30) and its biliary cancer module (QLQ-BIL21);Postoperative morbidity and mortality, as defined in Table 3, among patients who underwent combined extrahepatic bile duct and major liver resection. The International Study Group of Liver Surgery (ISGLS) definitions for post-hepatectomy liver failure, bile leakage and hemorrhage are used [14-16].

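### A non-significant primary result is read as no difference, and the preferred method is then selected from nine unranked secondary outcomes with no selection criterion

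*Protocol article*

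**What the plan says.** The protocol article, Secondary outcome measures, opens with a decision rule: the secondary outcomes "will be used to select the preferred method if there is no difference in the primary outcome" when the study concludes. Nine outcomes follow, without order or weights:

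1. preoperative cholangitis
2. procedures needed for technical success
3. therapeutic success 7 days after technical success
4. total stenting procedures
5. crossover
6. bilirubin decrease at 7 and 14 days
7. rescheduled or cancelled laparotomy
8. quality of life on two questionnaires
9. postoperative morbidity and mortality (Table 3) in resected patients

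Under Data analysis, the primary hypothesis is evaluated by a "Wilcoxon/Mann–Whitney rank-sum test with a two-sided 0.05 significance level". For the rest, "Subsequent analyses are directed at the secondary endpoints", with a test assigned by type of variable; for example, "Categorical variables will be evaluated using Pearson’s chi-squared test or Fisher’s Exact test as applicable". No significance level is given for these tests.

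Under Sample size, a 20% absolute decrease is named as the smallest that is clinically relevant. The Statistical analysis section adopts the intention-to-treat principle.

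**The concern.** Failing to reject in a superiority test does not show that two methods are alike. The protocol has no equivalence or non-inferiority margin for the primary outcome, so the condition in the rule can be met only by a non-significant test. The trial then moves from an inconclusive result to a named method.

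The move is unguarded in three ways.

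- **Selection.** With nine or more outcomes and no criterion, the choice can be made after the results are seen. Chance may favour either method, including the one with the worse primary estimate.
- **Conflict.** Nothing says what happens if, say, bilirubin favours one method and quality of life the other.
- **Population.** Therapeutic success is timed from technical success. The number of procedures to technical success has no natural value for a patient who never reaches it. Postoperative outcomes exist only after resection, and drainage complications can affect who reaches resection. A preference based on these outcomes leaves the intention-to-treat basis.

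At stake is the trial's recommendation, since the Discussion presents naming a preferred method as what the trial is for.

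**Working it through.** **1. The plan's own figure.** Inputs from Table 4: 0, 1 and ≥2 complications in 50/25/25% (EBD) and 75/17/8% (PTBD). I took two-sided 0.05, 80% power and 3% dropout, reading the printed α = 0.95 and β = 0.8 as confidence level and power. Simulating the tie-corrected rank-sum test (20,000 trials per size) gives 79.9% power at 51 per arm and 80.9% at 52. Then 51/0.97 = 52.6, rounded up to 53 per arm, or 106 in total, as stated. Closed formulas land within 2 patients per arm. The planned power is therefore about 80%, and 1 − 0.80 = 20% of trials with the planned effect end non-significant.

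**2. What a non-significant result would show.** Assume 53 per arm (the provisional size) and complication rates near 40%. The 95% half-width for the difference is 1.96 × √(2 × 0.40 × 0.60 / 53) = 0.187, about 19 points. An observed advantage for PTBD of as little as 2 points would give an interval reaching about 21 points, beyond the protocol's 20-point limit. Most non-significant results favouring PTBD would leave a relevant benefit open.

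**3. Number of comparisons.** The lower count is the nine listed items. The upper count is constructed: 5 single items + 2 bilirubin times ("Interval bilirubin decrease at 7 days and 14 days after biliary drainage relative to the bilirubin level at randomization") + 1 rescheduled or cancelled laparotomy + 6 quality of life (2 questionnaires, "EORTC Quality of Life Questionnaire C-30 (QLQ-C30) and its biliary cancer module (QLQ-BIL21"), at 3 post-baseline visits, one score each) + 10 Table 3 events (mortality and nine morbidities) = 24.

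**4. Chance of a false winner when the methods are equal.** This assumes 0.05 per secondary test and that any one significant result decides. The article states neither.

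Independent tests:

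- 9 tests: 1 − 0.95^9 = 0.370
- 24 tests: 1 − 0.95^24 = 0.708

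These are chances given a non-significant primary. The joint chance of a non-significant primary and at least one significant secondary is 0.95 × 0.370 = 0.351 and 0.95 × 0.708 = 0.673.

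Simulated with a common correlation among all the secondaries and the primary, given a non-significant primary:

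| Correlation | 9 tests | 24 tests |
|---|---|---|
| 0.3 | 32% | 59% |
| 0.5 | 25% | 44% |
| 0.7 | 17% | 28% |

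**5. Two qualifications.** Rare events under Fisher's exact test reject far less often than 5%. Assuming 25 resected patients per arm, the actual level is 0.1% at a 5% event rate and 0.9% at 10%. Setting the ten Table 3 tests at 2% or 1% gives 1 − 0.95^14 × 0.98^10 = 0.602 or 1 − 0.95^14 × 0.99^10 = 0.559, still assuming independence. Also, with independent tests, significant results point in opposite directions in about 4% (9 tests) and 20% (24 tests) of trials with a non-significant primary. Step 4 counts these as producing a winner, although no winner would be clear.

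**The case against.** The strongest reply is that the article never says one significant secondary outcome is enough. The rule could mean a joint clinical judgement across drainage success, quality of life and morbidity, which is a reasonable way to choose between two established techniques when the primary outcome is neutral. This stands as a limit on the numbers. A reader might infer that each secondary outcome is tested at 5%, that any one can name the winner, and that the plan therefore has a false-winner rate of 37–71%. The documents do not support that reading: 0.05 is stated for the primary only, no selection criterion is given, and nothing says that each Table 3 event or each questionnaire visit is tested separately. Independence is also implausible. Cholangitis is a component of the primary outcome, and the procedure counts and crossover are closely linked.

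A second reply is that the ordering of secondary outcomes and multiplicity control are commonly left to a full protocol or SAP, which is not shown. That is correct, and their absence alone would be no finding. But the article does state a rule, and as worded the rule turns a failed superiority test into a selection. The wording is what is at fault.

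A third reply is that under the planned effect, outcomes that overlap with the primary would tend to favour the better method. That is fair. The one-in-five figure assumes the planned effect and the false-winner figures assume equal methods, so they must not be combined. No rate of wrong selection under the planned effect has been calculated.

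**Conclusion.** The point holds as a badly fixed decision rule. It equates non-significance with no difference and sends the conclusion to nine unranked outcomes, some of which do not compare all randomized patients. That follows from the text and needs no calculation.

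The size of the error is conditional. If one secondary result at 0.05 sufficed, a false winner between equal methods would arise in at most about 37% (nine tests) or 71% (24 tests), with independence as the upper case. Under common correlation of 0.3–0.7 the figures are about 17–32% and 28–59%. All exceed 5% at least threefold, but they illustrate what the wording permits and are not an error rate of the plan. About one trial in five with the assumed effect would enter the rule. The primary test itself keeps its 5% level. The wording should be changed; the design need not be.

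**What to change.** Replace the opening sentence of Secondary outcome measures with:

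> If the primary comparison is not significant, superiority is not shown and the result is reported as inconclusive, with the 95% confidence interval for the difference in complication rate set against the 20-point limit of clinical relevance. Secondary outcomes are supportive and do not by themselves establish a preferred method.

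If the sponsor wants a formal secondary claim, it should pre-specify one key secondary outcome measured in all randomized patients and share the overall 0.05 between it and the primary. Testing it at a further full 0.05 after a failed primary would allow up to 1 − 0.95² = 9.75% overall under independence. Cholangitis is a weak candidate because it is already part of the primary outcome.

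The main change is wording, plus an absolute difference reported beside the planned relative risk. The downside is that the trial gives up naming a preferred method from any secondary outcome after a non-significant primary. The optional formal claim costs more: a smaller level for the primary lowers its power at 106 patients, so it would have to be allowed for when the definitive sample size is set.
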